**5.2 Precision Substudy:** The repeatability and reproducibility substudy will be performed including three cameras and three operators (see Section 3.2). A Latin Squares design (Supplementary Table 6) will be used with mixed effects models used to analyze the DDx algorithm outcome data on a log-scale with operator, camera, sequence, dilation, and FPRC as covariates. Separate analyses will be performed at the subject-level and at the eye-level. Each of 36 subjects, 50% positive for mtmDR in at least one eye, will have a total of 9 results on each eye (see protocol Section 9.4.1). Repeatability will be assessed within the three replicates from pre-specified camera-operator pairs, and reproducibility will be assessed from comparing results across the six camera-operator combinations. There will be 3 replicates on all 36 subjects (72 eyes) for 216 gradings for the replicate analyses and 6 measures on all 36 subjects (72 eyes) for 432 gradings for the reproducibility analysis.

[figure not shown]

|                     |               |        |              |
|---------------------|---------------|--------|--------------|
| CTMF-SA-DXSDR006-03 | SAP_2.1_clean | Rev. A | Pg. 13 of 16 |
|---------------------|---------------|--------|--------------|

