will involve capturing 4W and OCT retinal images by Fundus Photography Reading Center certified photographers, which together with the RV700 images will be transferred to retinal experts at a qualified reading center to determine the prognostic reference standard (PRS) for each eye, respectively ICDR grading for each eye. The study will reach its primary endpoints if the sensitivity and specificity of IDx-DR paired with the RV700 camera are substantially equivalent to those of the predicate device, IDx-DR.

In order to assure an adequate range of DR conditions in the study population sample, and avoid spectrum bias, for sensitivity and specificity analysis, the primary care study population will be enriched to ensure a sufficient range of diabetic retinopathy severity within cases. The enrichment cohort will be targeted using HbA1c levels.

A total of 36 subjects who participated in the Diagnostic Performance Study will be invited to participate in the Precision Substudy. Of these 36 subjects, 18 will have received a PRS determination of mtmDR(+) for at least one eye, and 18 will have received a PRS determination of mtmDR(-) for both eyes. Each participating subject will undergo a series of nine exams with three different RV700 cameras, three different operators, and three replicates to test the reproducibility and repeatability of using IDx-DR with the RV700.

All clinical study sites will have the adequate subject population and availability of space for at least one operator and one RV700 camera. This space needs to be able to be darkened. Two sites will need space for 3 camera operators and 3 RV700 cameras. Operators cannot have previous fundus imaging experience.

The overall study and the substudy analyses will be performed at both the eye-level and the subject-level for regulatory submission and publication consistent with the de novo study utilizing the Topcon NW400 retinal camera.

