#### 9.4. Precision Substudy

A repeatability and reproducibility substudy will be performed including three cameras, three operators, and three replicates. The unit of analysis will be the eye (two eyes included per subject). Each of 36 subjects, 50% positive for mtmDR in at least one eye, will have a total of 9 results on each eye (see Section 9.4.1). Select subjects will be invited for the Precision Substudy based on the PRS grading of their Diagnostic Performance Study images. Eighteen (18) of the Precision Substudy subjects will have received a grade of mtmDR(+) in at least one eye, and eighteen (18) will have received a grade of mtmDR(-) in both eyes. Subjects will be fully dilated and then undergo nine IDx-DR exams. The substudy will test three RV700 cameras and three operators with three replicates using a Latin Square design.

---

**Digital Diagnostics Confidential.** This document is intended for internal use only and may not be disclosed or reproduced in whole, or in part, for external distribution in any form without express written permission of DDx Legal. All hard copies should be checked against the current electronic revision prior to use and destroyed promptly thereafter. All hard copies are considered uncontrolled documents.

The camera, operator, and replicate combinations across subjects are specified below:

Exam A: RV700 A + Operator #1 (Replicate 1)  
 Exam B: RV700 A + Operator #2 (Replicate 1)  
 Exam C: RV700 A + Operator #2 (Replicate 2)  
 Exam D: RV700 B + Operator #2 (Replicate 1)  
 Exam E: RV700 B + Operator #3 (Replicate 1)  
 Exam F: RV700 B + Operator #3 (Replicate 2)  
 Exam G: RV700 C + Operator #1 (Replicate 1)  
 Exam H: RV700 C + Operator #1 (Replicate 2)  
 Exam I: RV700 C + Operator #3 (Replicate 1)

The Latin Squares design follows where the X represents an observation and R represents a replicate in order to estimate camera effect, operator effect, and reproducibility:

|          | Operator 1 | Operator 2 | Operator 3 |
|----------|------------|------------|------------|
| Camera A | X          | X, R       | -          |
| Camera B | -          | X          | X, R       |
| Camera C | X, R       | -          | X          |

Operators will reposition subjects between each imaging replicate. The order of the data collection will be recorded in the case report form.

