#### 9.4.1. Imaging Sequence for Precision Study

| Camera | Operator | Replicate |
|--------|----------|-----------|
| A      | 1        | 1         |
|        | 1        | 2         |
|        | 1        | 3         |
| B      | 2        | 1         |
|        | 2        | 2         |
|        | 2        | 3         |

---

**Digital Diagnostics Confidential.** This document is intended for internal use only and may not be disclosed or reproduced in whole, or in part, for external distribution in any form without express written permission of DDx Legal. All hard copies should be checked against the current electronic revision prior to use and destroyed promptly thereafter. All hard copies are considered uncontrolled documents.

|                      |   |    |
|----------------------|---|----|
| C                    | 3 | 1  |
|                      | 3 | 2  |
|                      | 3 | 3  |
| Total gradings / eye |   | 9  |
| Subjects per setting |   | 36 |

Endpoints for each analysis include mixed effects estimates of operator, camera, and replicate effects as well as overall agreement, average positive agreement, average negative agreement, and average ungradable agreement. Reproducibility, or inter-operator variability, will also be assessed based on agreement between three camera-operator pairs for a given subject (see Section 9.4.2). One-sided 97.5% confidence intervals for each endpoint will be computed using the clustered bootstrap approach. [12]

Data analysis will be performed using SAS (V9.3 or later).

Relevant data analyses will be repeated at the subject-level for regulatory submission and publication, consistent with the de novo study utilizing the Topcon NW400 retinal camera.

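### The Protocol 9.4.1 table pairs each camera with a single operator, which contradicts the six-pair Latin square stated everywhere else; if it were followed, camera and operator effects could not be separated

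*Combined protocol and SAP*

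**What the plan says.** **The six-pair scheme.** Protocol 9.4 lists exams A to I and lays them out as a grid: "The Latin Squares design follows where the X represents an observation and R represents a replicate". The occupied cells are A-1, A-2, B-2, B-3, C-1 and C-3, with A-2, B-3 and C-1 imaged twice. The same nine exams appear in Protocol 1.3.3 and 7.6, in SAP 3.2 and in SAP Supplementary Table 6. SAP 5.2 analyses them on that footing: "reproducibility will be assessed from comparing results across the six camera-operator combinations". It counts 216 gradings for the replicate analysis and 432 for reproducibility.

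**The three-pair scheme.** The table in Protocol 9.4.1 has camera A with operator 1 three times, B with 2 three times and C with 3 three times. The text below it says: "Reproducibility, or inter-operator variability, will also be assessed based on agreement between three camera-operator pairs for a given subject". The same paragraph states: "Endpoints for each analysis include mixed effects estimates of operator, camera, and replicate effects".

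**The cross-references.** Protocol 9.4 cites 9.4.1 for the nine results per eye. So does SAP 5.2, where each subject "will have a total of 9 results on each eye (see protocol Section 9.4.1").

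**A smaller mismatch.** The number of subjects per setting is 36 in Protocol 9.4.1 and 9 in SAP Supplementary Table 6.

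**The concern.** The substudy exists to say how much of the variation in the algorithm's output comes from the camera unit, how much from the operator and how much from plain repetition. That requires each camera to be used by more than one operator, and each operator to use more than one camera. The six-pair grid does this; the 9.4.1 table does not.

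A site or programmer who took 9.4.1 as the imaging plan would collect nine results per eye, exactly as expected, and would still lack the data for precision endpoints 1 and 6 as far as operator and camera are concerned. No later analysis could repair that. The risk of picking the wrong table is not remote. 9.4.1 is the section whose title announces the imaging sequence, two other sections cite it, and Protocol 1.3 points for the combinations to 1.3.2, which in the body of the protocol is the exam procedure.

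**Working it through.** **Inputs.** 36 subjects and two eyes each, so 36 × 2 = 72 eyes (SAP 5.2). Nine exams per eye under either scheme. Six-pair cells from Protocol 9.4 and SAP Supplementary Table 6; three-pair cells from Protocol 9.4.1.

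**1. The SAP's own counts.**

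- Six-pair scheme: 3 repeated cells × 72 = 216 replicate gradings; 6 distinct cells × 72 = 432 reproducibility gradings. Both SAP figures reproduce exactly.
- 9.4.1 table: 3 distinct pairs × 72 = 216 gradings between pairs; 6 extra replicates × 72 = 432. The two numbers come out the other way round.

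Both schemes total 9 × 72 = 648 gradings, so the total alone would not reveal which was used.

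**2. Can camera and operator be separated?** Take a model with an intercept m, camera effects b(B) and b(C) relative to camera A, and operator effects g(2) and g(3) relative to operator 1: five parameters.

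Expected values in the six-pair scheme:

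- A-1: m
- A-2: m + g(2)
- B-2: m + b(B) + g(2)
- B-3: m + b(B) + g(3)
- C-1: m + b(C)
- C-3: m + b(C) + g(3)

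Hence g(2) = A-2 minus A-1, b(B) = B-2 minus A-2, b(C) = C-1 minus A-1, and g(3) = C-3 minus C-1. All five parameters are determined. The design matrix has rank 5 of 5, with 2 degrees of freedom for camera given operator and 2 for operator given camera.

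Expected values under 9.4.1:

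- A-1: m
- B-2: m + b(B) + g(2)
- C-3: m + b(C) + g(3)

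The column for camera B is identical to the column for operator 2, and likewise camera C and operator 3. The rank is 3 of 5, with 0 degrees of freedom for either factor given the other. Only the sums b(B) + g(2) and b(C) + g(3) can be estimated. More replicates or subjects in the same three cells would not change this.

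Treating camera and operator as random does not help. The covariance structures for camera, operator and residual have rank 3 of 3 in the six-pair scheme and 2 of 3 under 9.4.1.

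**3. Exam codes.** Protocol 1.3.5 gives the example of the second replicate of operator 2 on camera A, coded C. Under 9.4.1 operator 2 never uses camera A. Only the first replicate in each of the three 9.4.1 pairs matches a code (A, D and I); the other six of the nine rows have none.

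**4. Subjects per setting.** The SAP's 216 and 432 require all 36 subjects in every setting. With 9 subjects per setting they would be 9 × 2 × 3 = 54 and 9 × 2 × 6 = 108. The 9 in SAP Supplementary Table 6 therefore conflicts with SAP 5.2. It equals the total of gradings per eye shown in the 9.4.1 table and may be a label slip, but the documents do not say so.

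**The case against.** The strongest reply is that the intended design is not in doubt. Six pairs appear in three protocol sections and in the SAP, the exam codes are built on them, and the SAP's counts work only with them. The revision histories record a move to the Latin square in the SAP and a modified substudy schema in the protocol, so 9.4.1 looks like a table that was not updated. This stands. It makes the point an inconsistency and the loss of estimability conditional. It does not remove the conflict: 9.4.1 is current text and other sections cite it.

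It is also fair to say that the damage would be limited. Under 9.4.1, positive, negative, ungradable and overall agreement could still be computed, although every between-pair comparison would change camera and operator together. The primary endpoints do not depend on the substudy.

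A reader might infer more than the documents support:

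- **That the SAP rests on the 9.4.1 layout.** It cites 9.4.1 only for nine results per eye and carries its own six-pair table.
- **That the dilation term is an error because every substudy subject is dilated.** The model is fitted "with operator, camera, sequence, dilation, and FPRC as covariates", and Protocol 7.6 allows re-dilation, so the term may vary. It is undefined, not shown to be wrong.
- **That two sites mean two people behind each operator label, and hence understated variability.** Protocol 4.1 says: "Two sites will need space for 3 camera operators and 3 RV700 cameras". It does not say that operators or cameras differ by site, or how they will be coded, so no size can be put on this.
- **That the exam order is defective.** No order is assigned in the design sections, but it is recorded and sequence is a covariate. A particular order would be a preference.

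**Conclusion.** Protocol 9.4.1 is wrong as written. Its table and its sentence on three pairs contradict the design stated in the rest of the protocol and in the SAP, and they contradict the separate operator and camera effects that 9.4.1 itself promises. If followed, the table gives rank 3 of 5 instead of 5 of 5, and the operator and camera parts of precision endpoints 1 and 6 are lost.

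The conflict between the passages is certain and rests on no assumption. The loss of estimability assumes that imaging actually follows 9.4.1 and that camera and operator enter as separate main effects, as SAP 5.2 plans. If exams A to I are run, the effects are separable and nothing is lost. The correction is necessary, but it concerns text and not the design the sponsor evidently intended.

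**What to change.** Before substudy imaging starts:

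1. Replace the table in Protocol 9.4.1 with the exam A to I table from Protocol 1.3.3.
2. In the reproducibility sentence of 9.4.1, replace the three pairs with the six camera-operator combinations, as in SAP 5.2.
3. Reconcile the subjects-per-setting entry between Protocol 9.4.1 (36) and SAP Supplementary Table 6 (9). The SAP's own grading counts imply 36.

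Two clarifications, not corrections, are worth adding to SAP 5.2 at the same time. If the two substudy sites use different operators or cameras, give each person and each unit a unique label nested within site. State also whether the dilation covariate means re-dilation during the session.

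The cost is wording in one protocol section, one SAP table entry and two clarifying sentences. No exam, subject or visit is added.

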#### 9.4.2. 3 by 3 Cross-Tabulation for Agreement Statistics

##### *Cross-Tabulation for Agreement Statistics*

|               | R2 Positive | R2 Negative | R2 Ungradable |
|---------------|-------------|-------------|---------------|
| R1 Positive   | PP          | PN          | PU            |
| R1 Negative   | NP          | NN          | NU            |
| R1 Ungradable | UP          | UN          | UU            |

R1 and R2 represent replicates 1 and 2

##### **Formulas:**

$$\text{Overall agreement (OA)} = \frac{PP+NN+UU}{\text{Total}}$$

$$\text{Average positive agreement (APA)} = \frac{2PP}{(PP+NP+UP)+(PP+PN+PU)}$$

$$\text{Average negative agreement (ANA)} = \frac{2NN}{(PN+NN+UN)+(NP+NN+NU)}$$

$$\text{Average ungradable agreement (AUA)} = \frac{2UU}{(PU+NU+UU)+(UP+UN+UU)}$$

---

**Digital Diagnostics Confidential.** This document is intended for internal use only and may not be disclosed or reproduced in whole, or in part, for external distribution in any form without express written permission of DDx Legal. All hard copies should be checked against the current electronic revision prior to use and destroyed promptly thereafter. All hard copies are considered uncontrolled documents.

## 10. Regulatory, Ethical, and Study Oversight Considerations

### **Ethical Considerations**

This study will be performed in accordance with the protocol and all applicable local regulatory requirements. The study will be conducted in accordance with the ethical principles that have their origins in the Declaration of Helsinki.

### **Institutional Review Board**

It is the responsibility of the Investigator to obtain the approval of the Institutional Review Board (IRB) before the start of the study. A copy of the approval letter will be supplied to the Sponsor, along with a roster of IRB members. During the course of the study, the Investigator or designee will provide timely and accurate reports to the IRB on the progress of the study at appropriate intervals (not to exceed 1 year) and at the completion of the study. Investigator or designee will notify the IRB of SAEs and/or UADE, or other important safety findings. The study protocol ICF information sheet advertisements (if any), and amendments (if any) will be approved by the IRB at each study site in conformance with CFR, Title 21, Part 56.

### **Subject Information and Consent**

Before the start of any study-related procedures are undertaken, the Investigator or designee must obtain written, informed consent from each study subject in accordance with US federal regulations (21 CFR §50) and the ICH document “Guidance for Industry – E6 Good Clinical Practice: Consolidated Guidance”. Informed consent will be obtained by discussing with the subject the purpose of the study, the risks and benefits, the study procedures, and any other information relevant to the subject.

The Investigator or designee must explain to the subject that for purposes of evaluating the study results, that subject’s private health information obtained during the study may be shared with the Sponsor, regulatory agencies, and IRBs, before enrolling that subject into the study. It is the Investigator’s (or designee’s) responsibility to obtain permission to use private health information per the Health Information Portability and Accountability Act (HIPAA) from each subject, or if appropriate, the subject’s legal representative.

The subject or his/her legal representative will document his/her informed consent by signing the current version of the written, IRB-approved ICF. The person who conducted the informed consent discussion with the subject and/or subject’s legal representative must also sign the ICF. The subject is given a fully executed copy of the ICF bearing all appropriate signatures, and the original must be maintained in the clinical study master files at the site.

---

**Digital Diagnostics Confidential.** This document is intended for internal use only and may not be disclosed or reproduced in whole, or in part, for external distribution in any form without express written permission of DDx Legal. All hard copies should be checked against the current electronic revision prior to use and destroyed promptly thereafter. All hard copies are considered uncontrolled documents.

The Investigator, or designee, is responsible for the content of the ICF, but the original and any updated versions must be approved by the Sponsor prior to submission to the IRB. The ICF should also include any additional information required by local laws relating to institutional review. All active subjects participating on the protocol must be re-consented each time the ICF is updated and re-approved by the IRB.

### **Investigator and Clinical Sites**

The Principal Investigator (PI) at each study site is the individual responsible for ensuring that the investigation is conducted according to the signed Investigator's statement, the protocol, and guidelines at their site. The PI at each clinical site will be responsible for the management of the study, which will include but not be limited to oversight of other designated study Investigators and study staff conducting any activities related to the study, maintenance of the study file and subject records, correspondence with the IRB, and completion of the electronic case report forms (eCRFs).

### **Data Monitoring**

Before the first subject is enrolled in the study, a Sponsor or CRO representative will meet with the Investigator and clinical site study staff to review the procedures for conducting the study and to train the staff on recording the data on the eCRFs using the EDC system. The Sponsor representative may periodically monitor the progress of the study by conducting on-site visits or virtual visits. The Sponsor representative will also be able to review data remotely, which may warrant more frequent communication with the Investigators and clinical site study staff. The Investigator will make available to the Sponsor representative the source documents, the signed consent forms, all other study-related documents, and the computer(s) that access the eCRFs. The Investigator or designee will be responsible for reviewing eCRFs, resolving data queries generated by the Sponsor or CRO, providing missing or corrected data, approving all changes to the data, and endorsing the subject data within the EDC system.

### **Data Management and Transfer**

Masking and privacy are essential data transfer and management elements during the study. The IDx-DR Client will securely transfer images captured from subjects to an analysis system that provides exam quality feedback results, housed, and maintained in a secure server. The study details on the data transfer and management responsibilities can be found in the Data Transfer Plan (DTP as well as the enrichment approach for the study. The DTP serves to designate data transfer and management responsibilities during the study's setup, during enrollment, and after the study to ensure data integrity and security, as referenced in Section 6.4. Additionally, the DTP describes the study data management and transfer responsibilities for the CRO, WRC, and the biostatistician while ensuring Digital Diagnostics remains masked in the study. The DTP also provides the details on the study's enrichment approach along with the personnel involved in the execution of the enrichment process.

---

**Digital Diagnostics Confidential.** This document is intended for internal use only and may not be disclosed or reproduced in whole, or in part, for external distribution in any form without express written permission of DDx Legal. All hard copies should be checked against the current electronic revision prior to use and destroyed promptly thereafter. All hard copies are considered uncontrolled documents.

### **Data Recording and Documentation**

Data collection will involve the use of the EDC system. In addition to periodic monitoring occurring within the system by CRO personnel, programmatic edit checks will be used to review the data for completeness, logic, and adherence to study protocol. As a result of this monitoring and these checks, queries may be issued to the clinical study site and answered by that study site.

Data will be stored and evaluated in such a way as to guarantee subject confidentiality in accordance with the legal stipulations applying to confidentiality of data. Study records (e.g., copies of eCRFs, regulatory documents, etc.) will be retained at the study site, along with adequate source documentation. All study records must be available for inspection by the Sponsor, and its authorized representatives.

